#### Final Assessment (T1)

Sixty days after baseline, patients undergo the predefined outcome assessment, including pain intensity, quality of life, pain interference, opioid consumption, adverse effects, and PREMs.

The primary analysis will compare baseline (T0) and 60-day (T1) assessments (Table 1). Information collected during routine follow-up will primarily be used for clinical monitoring and descriptive analyses.

**Table 1 table1:** Schedule of assessments and data collection time points.

Variable	Baseline (T0)	Routine clinical follow-up	60 days (T1)
Informed consent	✓		
Demographics	✓		
Cancer characteristics	✓		
VAS^a^	✓	✓	✓
EQ-5D	✓		✓
BPI-SF^b^	✓		✓
DMED^c^	✓	✓	✓
Adverse effects	✓	✓	✓
PREMs^d^ (satisfaction)			✓
Committee recommendations	✓		
Implementation of recommendations		✓	✓

^a^VAS: visual analog scale.

^b^BPI-SF: Brief Pain Inventory–Short Form.

^c^DMED: daily morphine equivalent dose.

^d^PREM: patient-reported experience measure.

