### Study Outcomes

The primary outcome is the change in pain intensity, measured using the VAS, from baseline (T0) to 60 days (T1) following multidisciplinary committee assessment. A reduction of at least 1 point on the VAS was predefined as the minimal clinically important difference, based on previous literature in patients with cancer-related pain [31]. This threshold was used for the sample size calculation and will also serve to interpret the clinical relevance of the observed changes.

Secondary outcomes include changes between T0 and T1 in health-related quality of life measured using the EQ-5D [32], pain-related functional interference assessed with the Brief Pain Inventory–Short Form (BPI-SF) [33], DMED, analgesic treatment–related adverse effects, and PREMs, including satisfaction with care assessed using a Likert-scale questionnaire at T1.

Table 2 summarizes the study outcomes, instruments, and time points. The primary analysis will focus on paired comparison of VAS scores between T0 and T1. Secondary outcomes listed in Table 2 will be analyzed accordingly based on variable type and distribution.

**Table 2 table2:** Study outcomes.

Outcome category	Variable	Instrument or source	Time points	Type
Pain intensity	VAS^a^ score (0-10)	VAS	T0 and T1	Primary
Quality of life	EQ-5D index score	EQ-5D questionnaire	T0 and T1	Secondary
Pain interference	BPI-SF^b^ interference score	BPI-SF	T0 and T1	Secondary
Opioid consumption	Daily morphine equivalent dose (mg/day)	Clinical record	T0 and T1	Secondary
Adverse effects	Presence or absence and type	Clinical assessment	T0 and T1	Secondary
Committee recommendation	Type of recommendation issued	Committee record	T0	Descriptive
Implementation of recommendations	Implementation status (implemented, partially implemented, or not implemented)	Electronic medical record	T1	Exploratory
Patient satisfaction	Likert-scale satisfaction score	PREM^c^ questionnaire	T1	Secondary

^a^VAS: visual analog scale.

^b^BPI-SF: Brief Pain Inventory–Short Form.

^c^PREM: patient-reported experience measure.

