### Recruitment and Study Procedures

#### Patient Eligibility Criteria

##### Inclusion Criteria

Inclusion criteria include adults aged ≥18 years with active cancer, defined as histologically confirmed malignant disease receiving active antineoplastic treatment or with documented disease progression; moderate to severe cancer-related pain (VAS ≥4); presentation to the multidisciplinary cancer pain management committee; ability to understand study procedures in Spanish or Galician; and provision of written informed consent.

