#### Statistical Analysis Plan

Statistical analyses will be performed using SPSS (IBM Corp) or equivalent statistical software. Baseline demographic and clinical characteristics will be summarized using appropriate descriptive statistics. Variables of interest will include age, sex, cancer type, tumor stage, presence of metastatic disease, ongoing oncological treatment, baseline opioid use (DMED), previous interventional pain procedures, and palliative care status. A 2-sided *P* value of <.05 will be considered statistically significant. Given the exploratory nature of secondary outcomes, no formal adjustment for multiple comparisons will be applied; therefore, secondary analyses will be interpreted cautiously.

Categorical variables will be summarized as frequencies and percentages. Continuous variables will be described using means and SDs or medians and IQRs, depending on data distribution.

Normality of continuous variables will be assessed using the Shapiro-Wilk test to determine the appropriate statistical test.

For the primary outcome, VAS scores at baseline (T0) and at 60 days (T1) will be compared using paired *t* tests or Wilcoxon signed rank tests, as appropriate. Mean changes in VAS scores will be reported together with 95% CIs and standardized effect sizes (Cohen *d*) to facilitate interpretation of both statistical and clinical significance.

Secondary pre-post comparisons for continuous variables (eg, EQ-5D scores, BPI-SF scores, and DMED) will be analyzed using the same approach. Categorical variables, including adverse effects and selected PREMs, will be analyzed using chi-square or McNemar tests, as appropriate. Because pain outcomes may be influenced by patient and disease characteristics, exploratory multivariable regression analyses will be performed to evaluate the association between multidisciplinary committee assessment and changes in pain intensity after adjustment for clinically relevant covariates. Prespecified candidate covariates will include age, sex, cancer type, tumor stage, metastatic disease, baseline VAS score, baseline opioid consumption, ongoing oncological treatment, interventional pain procedures, and palliative care status.

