Because of the observational design, the relatively small sample size, and the exploratory nature of these analyses, adjusted regression models will be considered hypothesis-generating and interpreted with appropriate caution. Predefined exploratory subgroup analyses will be performed whenever sample size permits. These analyses may include comparisons according to cancer type, metastatic vs nonmetastatic disease, baseline pain severity (moderate vs severe), and patients who are receiving palliative vs nonpalliative care. These subgroup analyses will be considered exploratory and interpreted cautiously.

Analyses will primarily be conducted using complete-case analysis. The frequency, pattern, and potential reasons for missing data will be described. In patients with advanced cancer, missing outcome data may result from clinical deterioration, hospitalization, or death and may therefore be informative (missing not at random). If missing data for the primary outcome exceed 5%, multiple imputation will be considered only as part of sensitivity analyses and only if the missing-data mechanism is considered reasonably compatible with the missing-at-random assumption. The results of any imputation-based analyses will be interpreted cautiously in light of the potential for informative missingness. Additional sensitivity analyses, including complete-case analyses, will be performed whenever appropriate to assess the robustness of the primary findings. All analyses will follow the predefined statistical plan approved by the research ethics committee.

As this is an observational study protocol rather than a clinical trial, the manuscript was primarily prepared in accordance with the STROBE (Strengthening the Reporting of Observational Studies in Epidemiology) statement [34]. Elements of the SPIRIT (Standard Protocol Items: Recommendations for Interventional Trials) statement were considered where applicable to improve protocol transparency [35].

A participant flow diagram will be used to describe progression through the study, including numbers assessed for eligibility, enrolled, completing follow-up, and included in the final analysis.

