### Strengths and Limitations

Strengths of this protocol include its prospective observational design, prospective protocol registration, consecutive patient recruitment, standardized outcome assessment, and evaluation of both clinical and patient-reported outcomes under routine clinical conditions. Furthermore, the multidisciplinary nature of the committee reflects contemporary recommendations for the management of complex cancer-related pain.

Several limitations should also be acknowledged. Because of the observational pre-post design and the absence of a control group, causal inference regarding the effect of multidisciplinary committee assessment cannot be established. Changes in pain intensity may also be influenced by regression to the mean, the natural course of the underlying disease, disease progression or response to oncological treatment, medication adjustments, or other concurrent clinical interventions occurring during follow-up. In addition, the single-center design may limit external validity, and residual confounding cannot be completely excluded despite planned exploratory adjusted analyses.

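### The planned moderate-versus-severe subgroup is formed on the T0 VAS; if change from T0 is compared between those groups, regression to the mean alone makes severe pain appear to improve more

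*Protocol article*

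**What the plan says.** The Statistical Analysis Plan section of the protocol article names possible subgroup comparisons, among them "metastatic vs nonmetastatic disease, baseline pain severity (moderate vs severe". It gives no cut-point and does not say which outcome is compared. It adds: "These subgroup analyses will be considered exploratory and interpreted cautiously".

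The outcome that the plan builds on is defined under Study Outcomes: "The primary outcome is the change in pain intensity, measured using the VAS, from baseline (T0) to 60 days (T1". A 1-point reduction is the minimal clinically important difference there. Entry requires "moderate to severe cancer-related pain (VAS ≥4". Table 1 schedules VAS at T0, during routine follow-up and at T1, with no separate screening value. The main test is paired: "VAS scores at baseline (T0) and at 60 days (T1) will be compared using paired".

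Strengths and Limitations acknowledges the general problem: "Changes in pain intensity may also be influenced by regression to the mean". That sentence concerns the cohort's change as a whole. Nothing links it to the severity subgroup. Baseline VAS appears as a candidate covariate, but only in the exploratory regression.

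**The concern.** A single VAS reading mixes a patient's usual pain with day-to-day variation and measurement error. Patients who score high at T0 include more who happened to be above their usual level, and these tend to score lower at T1. Patients in the moderate band contain fewer of them. When T0 both assigns the group and starts the change score, the two groups differ in expected change without any difference in benefit.

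The likely result is a report that patients with severe pain gained more after committee assessment. A reader could take that as a reason to direct referrals by severity, although the pattern would have arisen under no change at all.

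**Working it through.** **Inputs from the article.** VAS 0–10; entry at 4 or above; 64 evaluable patients; SD 2; important difference 1 point.

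**Assumptions, because the article is silent.** Cut between moderate and severe at 7; mean VAS of the referred population μ = 5, 6 or 7; T0–T1 correlation ρ = 0.3, 0.5 or 0.7; normal scores with the same mean and SD at both visits, so true change is zero.

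**The plan's own figure.** 64/0.95 = 67.4, so 68 follows from 64. The article does not say whether SD 2 is the SD of a VAS score or of the change. As the SD of change, a paired calculation gives (1.960 + 0.842)² × 2²/1² = 31.4, so 32 (34 with the t distribution). As a per-visit SD with ρ = 0, the SD of change is 2√2 = 2.83 and n is 63 (65 with t), close to 64. I therefore take SD 2 as per visit. At ρ = 0.5 the two readings coincide in an unselected population, since 2 × √(2 × 0.5) = 2.

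**Step 1: expected drop at a given T0.** With zero true change, E[T1 | T0 = x] = μ + ρ(x − μ), so the expected drop is (1 − ρ)(x − μ). It rises with T0 whenever ρ is below 1.

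**Step 2: mean T0 in each group.** For a normal score restricted to a–b, the mean is μ + 2 × [φ(A) − φ(B)]/[Φ(B) − Φ(A)], with A = (a − μ)/2 and B = (b − μ)/2. For μ = 6:
- severe (7 or above): 6 + 2 × 0.3521/0.3085 = 8.28
- moderate (4 to below 7): 6 + 2 × (0.2420 − 0.3521)/(0.6915 − 0.1587) = 5.59

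**Step 3: false gap** = (1 − ρ) × (severe mean T0 − moderate mean T0). For μ = 6 and ρ = 0.5: 0.5 × 2.70 = 1.35 points.

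| μ | Severe mean T0 | Moderate mean T0 | Difference | Gap at ρ 0.3 / 0.5 / 0.7 | False significance at n = 64 |
|---|---|---|---|---|---|
| 5 | 8.05 | 5.41 | 2.64 | 1.85 / 1.32 / 0.79 | 85% / 67% / 43% |
| 6 | 8.28 | 5.59 | 2.70 | 1.89 / 1.35 / 0.81 | 94% / 81% / 55% |
| 7 | 8.60 | 5.76 | 2.84 | 1.99 / 1.42 / 0.85 | 97% / 87% / 61% |

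The last column is from simulation: the share of samples in which a pooled t test of change favours the severe group at two-sided 5%, where 2.5% would be expected in that direction. Clipping scores to 0–10 changes the results little. At ρ = 0.8 the gap is 0.53 to 0.57 points and false significance 30% to 44%.

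**Step 4: would a separate VAS remove it?** If an earlier VAS forms the groups and its correlation with T0 equals its correlation with T1, the gap vanishes (within about ±0.02 points in simulation). If the correlation fades with time, a gap remains. With 0.7 to T0 and 0.5 or 0.4 to T1, at μ = 5, it is (0.7 − 0.5) × 2.64 = 0.53 or (0.7 − 0.4) × 2.64 = 0.79 points.

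**Step 5: the whole sample.** If the T0 score is also the qualifying score, the spurious mean drop is (1 − ρ)(E[T0 | T0 ≥ 4] − μ). For ρ from 0.7 to 0.3:
- μ = 5: 0.31 to 0.71 points (mean T0 6.02)
- μ = 6: 0.17 to 0.40 points (6.58)
- μ = 7: 0.08 to 0.19 points (7.28)

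The chance of a significant drop at n = 64 is 37% to 75%, 14% to 30% and 6% to 10% respectively. This result is governed by the unknown μ. The severity gap hardly depends on it.

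**The case against.** **The subgroup is optional and exploratory.** It is run only if numbers permit, its outcome and cut are not stated, and such detail may sit in the preregistered analysis plan, which is not shown. This stands as a limit: the point is conditional on change being the outcome compared. But the label guards against chance findings, and caution does not remove a bias whose direction is known in advance.

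**Baseline VAS is already a regression covariate.** True, and it makes the remedy easy. It does not protect a separate comparison of change by T0 category.

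**A false severity finding is not certain.** Correct: at ρ = 0.7 and a mean of 5 or 6, false significance is 43% to 55%.

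**A stronger reading is tempting:** that the primary paired test is itself invalid because patients qualify on the score from which change is measured. The documents do not support that. No section says that the qualifying VAS is the T0 VAS; Recruitment and Informed Consent places the invitation after committee discussion, so an earlier clinical value could be the one used. The aim is descriptive, regression to the mean is disclosed, and the article says that given "the absence of a control group, causal inference regarding the effect of multidisciplinary committee assessment cannot be established". A drop that includes regression to the mean is still the observed change. The severity problem does not need that premise: a split on T0 is affected even if eligibility rests on another reading.

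**Conclusion.** The point holds for the severity subgroup, provided that change from T0 is what is compared. With no true change, the severe group would appear to improve by about 0.8 to 2.0 points more than the moderate group, and by more than the plan's 1-point threshold at correlations of 0.5 or less. This rests on SD 2 per visit, a cut at 7, a referral mean of 5 to 7 and a correlation of 0.7 to 0.3, none of which the article settles. The direction holds for any correlation below 1.

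For the whole-sample test the conclusion is only a caution: neither the P value nor the 1-point threshold should be read as change attributable to the committee. The article already says most of this.

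**What to change.** 1. Remove the comparison of raw change between moderate and severe T0 groups. Replace it with a model of T1 VAS on continuous T0 VAS, reporting expected T1 across the range of T0.
2. State beforehand that a slope below 1 is expected from regression to the mean and does not show greater benefit in severe pain. The same applies to the baseline VAS coefficient if the exploratory regression keeps change as its outcome.
3. If a VAS documented at referral exists in the clinical record, record it and use it as a sensitivity grouping, noting that it reduces the artefact but may not remove it.
4. Add one sentence to the reporting of the primary result that carries over the caution from Strengths and Limitations.

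Eligibility need not change. Nor would I subtract a calculated regression-to-the-mean drop based on the observed correlation. Truncation at VAS 4 attenuates that correlation (a true 0.5 appears as 0.37 to 0.42 at means 5 to 6), and the calculation also needs an unselected mean and SD that the study does not plan to collect.

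The cost is analysis wording and, for item 3, one field taken from the record. With 3 participants enrolled at submission of the revised manuscript, this is easy to do now. The loss is the simple moderate-versus-severe comparison of change.

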##### Exclusion Criteria

Exclusion criteria include patients with severe cognitive impairment, dementia, intellectual disability, or any other condition preventing reliable completion of study assessments; patients in the agonal phase or with an expected survival insufficient to complete follow-up; refusal or inability to provide written informed consent.

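### The plan foresees T1 pain scores missing not at random, but the only robustness check it names for that case is the complete-case analysis that is already primary

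*Protocol article*

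**What the plan says.** All the rules on missing data stand in one paragraph of the protocol article, under Statistical Analysis Plan:

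- Primary approach: "Analyses will primarily be conducted using complete-case analysis".
- Description: "The frequency, pattern, and potential reasons for missing data will be described".
- Expected mechanism: in advanced cancer, "missing outcome data may result from clinical deterioration, hospitalization, or death and may therefore be informative (missing not at random".
- Imputation, first condition: "If missing data for the primary outcome exceed 5%, multiple imputation will be considered only as part of sensitivity analyses".
- Imputation, second condition: "only if the missing-data mechanism is considered reasonably compatible with the missing-at-random assumption".
- Other checks: "Additional sensitivity analyses, including complete-case analyses, will be performed whenever appropriate to assess the robustness of the primary findings".

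Three other places bear on the point. Table 1 schedules VAS and DMED at routine follow-up as well as at T0 and T1, and the section Final Assessment (T1) adds: "Information collected during routine follow-up will primarily be used for clinical monitoring and descriptive analyses". The exclusion criteria remove "patients in the agonal phase or with an expected survival insufficient to complete follow-up". The sample size section allows for 5% dropout, the only quantity the article gives for expected loss.

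**The concern.** A sensitivity analysis for missing data should change the assumption on which the primary result rests. Here the primary result rests on the T1 completers, and the plan itself says that absence at T1 may be linked to deterioration or death. In that situation the second condition rules imputation out, and the remaining named check repeats the primary analysis. A report could follow this plan to the letter and claim robustness from comparing an analysis with itself.

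The primary objective is to describe the change in pain in the patients assessed by the committee. Selective loss therefore acts directly on the quantity being described, and disclaiming causal inference does not remove it. If patients lost through deterioration have worse pain than those who stay, which is plausible but not quantified in the article, the completer mean overstates improvement. The result is to be read against a predefined 1-point important difference, so an error of a few tenths of a point could change its clinical interpretation.

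**Working it through.** **1. The plan's own figure.** Evaluable patients 64, dropout 5% (sample size section): 64 / 0.95 = 67.4, rounded up to 68. This reproduces the stated total.

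**2. Where the 5% trigger falls.** 0.05 × 68 = 3.4. Three missing T1 scores (3/68 = 4.4%) stay below the trigger; the fourth (4/68 = 5.9%) passes it. The trigger therefore sits at the loss the plan already anticipates.

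**3. What the rule names in each case.**

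| T1 VAS missing | Mechanism judged | Primary | Named sensitivity analyses |
|---|---|---|---|
| 0–3 of 68 | any | complete-case | complete-case |
| 4 or more | missing at random plausible | complete-case | multiple imputation (considered); complete-case |
| 4 or more | missing at random not plausible | complete-case | complete-case |

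Only the middle row contains an analysis that can differ from the primary. The last row is the case the plan warns about.

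**4. Illustrative size.** Inputs: N = 68 (document); completer mean change −1.0, set equal to the important difference (assumption); number missing k (assumption, except the 5% row); δ = how many points worse the missing patients do than completers (assumption, 2 or 3).

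Mean over all 68 = [(68 − k)(−1) + k(−1 + δ)] / 68 = −1 + kδ/68. The overstatement by completers is kδ/68.

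| Missing | k | Overstatement, δ = 2 | Overstatement, δ = 3 | Mean, δ = 2 | Mean, δ = 3 |
|---|---|---|---|---|---|
| about 5% | 3 | 6/68 = 0.09 | 9/68 = 0.13 | −0.91 | −0.87 |
| about 5% | 4 | 8/68 = 0.12 | 12/68 = 0.18 | −0.88 | −0.82 |
| 10% | 7 | 14/68 = 0.21 | 21/68 = 0.31 | −0.79 | −0.69 |
| 20% | 14 | 28/68 = 0.41 | 42/68 = 0.62 | −0.59 | −0.38 |
| 30% | 20 | 40/68 = 0.59 | 60/68 = 0.88 | −0.41 | −0.12 |

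With completers at −1.0, δ = 2 means the missing patients worsen by 1 point from baseline, and δ = 3 by 2 points. If the missing patients are merely unchanged (δ = 1), the overstatement is about 0.05, 0.10, 0.20 and 0.30 points at 5%, 10%, 20% and 30% missing.

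In every row the mean is still an improvement, so what moves is its position relative to 1 point. The arithmetic gives every missing patient a T1 value, so it applies only to patients alive at T1 whose score is absent. It is not a statement about patients who died.

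**The case against.** **The condition on imputation is correct in itself.** Standard multiple imputation assumes missing at random and would not remove bias from informative missingness. A reader might infer that the condition is the error and that deleting it would cure the problem. It would not, and that reading is not supported. The defect is the absence of anything in its place.

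**The plan is not silent.** It promises to describe the amount, pattern and reasons for missing data, warns openly of informative missingness, and plans a flow diagram. Its list of further sensitivity analyses is worded as open. A reader might infer that the bias can never be examined; the text supports only that no named analysis examines it.

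**Follow-up scores are not barred from modelling.** The article says they will be used primarily, not solely, for monitoring and description. Those contacts also follow clinical need, so their timing may itself be informative.

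**A fuller plan exists.** The article refers to a statistical plan approved by the ethics committee and preregistered. Delta values and imputation models could properly sit there, and their absence from the article is no fault. But the article does state the rule, its trigger, its condition and its named check. The objection is to that stated rule, and naming the primary analysis as a check on itself is an error wherever the details are kept.

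**The loss may be small.** The exclusion for short expected survival should reduce deaths, and at 5% loss the overstatement is minor. This stands for the size. It does not repair the rule, because the plan still foresees informative loss and provides for more than 5% missing.

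**Conclusion.** The point holds in this form: in the missing-not-at-random case that the plan foresees, no analysis it names can differ from the primary one, so robustness cannot be shown. That part rests on the text alone.

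The size rests on assumptions. With completers improving by 1.0 point and missing patients 2 to 3 points worse than completers, the overstatement is 0.09–0.18 points at the plan's own 5% loss, 0.21–0.31 at 10%, 0.41–0.62 at 20% and 0.59–0.88 at 30%. A reader might take the upper figures as the expected bias. The documents do not support this: they give no missing share beyond 5% and no figure for how missing patients fare, and they say only that missingness may be informative. The direction, towards overstated improvement, is likewise an inference from the causes the plan lists.

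The rule should be corrected. The fault does not undermine the design, and with 3 participants enrolled at submission of the revised manuscript there was still time to correct it before outcome data accumulate.

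**What to change.** 1. Remove complete-case analysis from the list of sensitivity analyses.
2. Prespecify, whatever the percentage missing, one missing-at-random analysis as the reference: a mixed model or multiple imputation using T0 data and, where available, routine follow-up VAS and DMED. State that the timing of those follow-up contacts depends on clinical need.
3. Build on it a delta-adjusted tipping-point analysis among patients alive at T1. Worsen imputed T1 VAS by 0, 1, 2 and 3 points. Report the delta at which mean improvement falls below 1 point and the delta at which the confidence interval includes 0. Here delta is a shift from the imputed value; it matches δ in the table only if imputations centre on the completers' mean change.
4. Report deaths before T1 as a separate count and impute no VAS for them.
5. Keep the statement that unadjusted imputation relies on missing at random, as a guide to interpretation and not as a condition for running items 2 and 3.

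Cost: plan wording and modest programming on data already scheduled for collection. The sample size does not change. The reported result may look less favourable.
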